#### **S. 3.3.7. Data collection procedures**

Male smokers will be recruited in the Obstetrics and Gynecology clinics at tertiary public hospitals in China when the males accompany with their partners to have a body check. Invitation letter will be sent to the public hospitals to participate in this study. After obtain the permission of these hospitals. These eligible people were invited to participate in the study after telling the purpose of this study. They will be given the option of participating or refusing and will be told that their participation is voluntary without prejudice. Written consent will be obtained from those subjects accepting to receive the interventions.

After the consent is obtained, the participant will be coded. By using a computer random selection procedure from the code, the participants will be randomly allocated into three arms, which are intervention group 1, intervention group 2 and control group. The subjects' demographic information, smoking characteristics, self-efficacy level, and exhaled carbon monoxide (CO) level at the baseline will be assessed by the research nurses. The biochemical validation will be done by a staff member who has not delivered the intervention and conducted the telephone counselling follow-up. Yet all subjects will not be blinded, because they will receive the behavioral intervention.

In the intervention group, the smokers will receive an intervention including video, brief advice, and pamphlet. In the intervention group 2, the subjects will text message, brief advice and pamphlet. For the participants in the control group, they will only receive a brief advice and pamphlet materials at the baseline. The detail procedure of data collection is presented in the figure 2 below.

#### **S. 3.4. Data analysis**

The IBM SPSS Statistics (SPSS: Version 20.0; SPSS Inc., Chicago, IL, USA) for windows will be used for data analysis. A p-value  $<0.05$  was considered as statistically significant. Descriptive statistics will be used to calculate the frequency and percentage (categorical data) or the mean and standard deviations (continuous data) of different demographic and social-economic characteristics. The intention-to-treat (ITT) principle will be used for outcome comparison between groups. Information missed at follow-up will be considered as non-quitters, non-reducers or do not use the video if no records about watching full video set. Multiple imputation will be used to fill the missing value of the demographic information at baseline. One-way ANOVA test or Mann-Whitney test and chi-square test will be used to compare the differences of nicotine dependency, stage of readiness to quit, and self-efficacy among three groups between baseline and 6-month follow-up for those who continued smoking. Logistic multiple regression will be conducted to examine the association between the intervention and the outcomes at 6-month follow-up. Subgroup analysis will be

performed by the first time to be father, level of nicotine dependence, and readiness to quit at baseline.

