#### *S. 3.3.3.2. Smoking characteristics*

The baseline of smoking characteristics will be collected through a structured questionnaire set. The content of the structured questionnaire set will include the, levels of daily cigarette consumption, history of past quit attempts, nicotine dependency assessed by the Fagerstrom Test of Nicotine Dependence.

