#### *S.3.3.3.4. Smoking Self-efficacy Questionnaire (SEQ-12)*

Self-efficacy of participants against tobacco will be assessed by using by the SEQ-12. The SEQ-12 is categorized into two subscales, namely internal stimuli (6 items) and external stimuli (6 items), with total possible scores ranging from 6 to 30 for both internal stimuli and external stimuli. Higher scores of the SEQ-12 on both subscales indicate greater self-efficacy to refrain from smoking.

The psychometric properties of this scale have been empirically examined with the Cronbach's alpha coefficients of 0.95 and 0.94 for internal stimuli and external stimuli, respectively, indicating excellent internal consistency. The intraclass correlation coefficients were 0.95 and 0.93 for internal stimuli and external stimuli, respectively, demonstrating excellent test-retest reliability[2].

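### A two-sample test, Mann-Whitney, is named for a three-arm comparison of nicotine dependence, readiness and self-efficacy; these analyses of continuing smokers need a three-group test, baseline adjustment and an exploratory label

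*Protocol*

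**What the plan says.** S. 3.3.7 (Data collection procedures) sets up the comparison: "the participants will be randomly allocated into three arms, which are intervention group 1, intervention group 2 and control group".

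S. 3.4 (Data analysis) then names the tests for three measures, namely nicotine dependence, stage of readiness to quit and self-efficacy: "One-way ANOVA test or Mann-Whitney test and chi-square test will be used to compare the differences of nicotine dependency". The same sentence ends by saying how and in whom they are compared: "among three groups between baseline and 6-month follow-up for those who continued smoking". The section gives a single significance threshold of 0.05. It does not mention Kruskal-Wallis, pairwise testing, a multiplicity rule or baseline adjustment for these measures. A multiple logistic regression is named separately for the 6-month outcomes, without a covariate list.

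Baseline values of all three measures are available:
- **Nicotine dependence:** S. 3.3.3.2 lists "nicotine dependency assessed by the Fagerstrom Test of Nicotine Dependence" among the baseline smoking characteristics.
- **Self-efficacy:** S. 3.3.7 says "The subjects' demographic information, smoking characteristics, self-efficacy level, and exhaled carbon monoxide (CO) level at the baseline will be assessed". The SEQ-12 gives two subscales, with "total possible scores ranging from 6 to 30 for both internal stimuli and external stimuli".
- **Readiness:** collection at baseline is implied by the planned subgroups, which include "level of nicotine dependence, and readiness to quit at baseline".

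**The concern.** The sentence offers Mann-Whitney as the rank alternative to one-way ANOVA. One-way ANOVA handles three groups and Mann-Whitney handles two, so anyone who takes the rank route cannot carry out the stated comparison as written. The rank route is a plausible choice here: the protocol's own description of the FTND calls it ordinal, and readiness is recorded as a stage. The analyst would have to choose between substituting another test, running three pairwise tests without a stated error rule, and picking one pair after seeing the data.

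The second issue is how baseline enters. If the sentence means change from baseline, it passes over a more precise analysis that uses data already collected. A change score is also negatively correlated with baseline whenever the baseline-to-6-month correlation is below 1, so a chance imbalance at baseline carries into the comparison.

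The third issue limits what any choice of test can achieve. Whether a man is still smoking at 6 months is itself a result of the trial. Arms compared within that subset are no longer the arms that were randomised.

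**Working it through.** The protocol gives no figure for these analyses. Its sample size (264 per group, 990 in total) concerns the binary quit rate and does not enter here.

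**1. Does the named test fit the comparison?**

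| Item | Protocol | Groups |
|---|---|---|
| Arms to be compared | S. 3.3.7 and S. 3.4 | 3 |
| One-way ANOVA | S. 3.4 | 2 or more |
| Chi-square | S. 3.4 | 2 or more |
| Mann-Whitney | S. 3.4 | exactly 2 |

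Only Mann-Whitney fails to match. Its counterpart for three groups is Kruskal-Wallis.

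**2. What if Mann-Whitney is applied pair by pair?** Three arms give three pairs. With each pair tested at 0.05 and no true difference anywhere:
- If the three tests were independent: 1 − (1 − 0.05)³ = 1 − 0.857 = 0.143. This is an upper figure, because each two pairs share an arm.
- Three pairwise z-tests among equal arms, allowing for the shared arms, simulated with 1.5 million draws: 0.122.
- Three actual Mann-Whitney tests, 200 men per arm, 5,000 simulated trials: 0.120.
- One Kruskal-Wallis test on the same simulated trials: 0.047.

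Unadjusted pairwise use therefore gives about 12%, and a single three-group test stays near 5%.

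**3. Change score against ANCOVA.** Assume the same variance σ² at baseline and 6 months, and correlation rho between them.
- Variance of the change score: 2σ²(1 − rho).
- Residual variance of the 6-month score given baseline: σ²(1 − rho²).
- Ratio of ANCOVA to change score: (1 − rho²) / [2(1 − rho)] = (1 + rho)/2.

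| rho (assumed) | Change, ÷σ² | ANCOVA, ÷σ² | Ratio |
|---|---|---|---|
| 0.3 | 1.40 | 0.91 | 65% |
| 0.5 | 1.00 | 0.75 | 75% |
| 0.7 | 0.60 | 0.51 | 85% |
| 0.8 | 0.40 | 0.36 | 90% |
| 0.93 | 0.14 | 0.1351 | 96.5% |
| 0.95 | 0.10 | 0.0975 | 97.5% |

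The last two rows use the SEQ-12 test-retest coefficients quoted in S. 3.3.3.4. They describe reliability, not the correlation over 6 months in a cessation trial, so they serve only as the high end of the range. The protocol gives no comparable figure for the FTND.

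**4. Which outcomes are touched?** S. 3.3.6 lists the self-reported quit rate at 6 months as primary. Its secondary outcomes are validated abstinence, reduction in consumption and readiness. Of the three measures in the sentence, only readiness is listed; FTND and self-efficacy are not listed as outcomes.

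**The case against.** The strongest reply is that Mann-Whitney is a slip of the pen for Kruskal-Wallis, and that the slip has no error-rate consequence. This largely stands as regards intent. A reader might infer that the trial will run at a 12% error rate, but nowhere does the protocol say that three unadjusted pairwise tests will be done. The 12% is what follows if that route is taken. The reply does not remove the fault, because the named test does not fit the comparison and no rule says what replaces it.

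A second reply is that change scores are legitimate and that covariate choice belongs in a statistical analysis plan. This also stands in part. It is tempting to say that the plan throws the baseline away. It does not: a change score uses the baseline with its slope fixed at 1 and is valid in a randomised comparison. Even the change-score reading is only the likeliest one, since the sentence could also mean group differences at each time point. Nor do the documents support a single headline such as a third more patients. That figure is 1/0.75 = 1.33 at rho 0.5 alone, and the gain falls to about 3% near 0.95. What remains is that ANCOVA has the smaller variance at every correlation below 1, and the data for it are already collected.

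A third reply is that the reach is small, and it is. A reader might extend the problem to the main conclusion of the trial, but the sentence does not govern the primary quit rate.

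Finally, a reader might suppose that the right test makes this comparison sound. It does not. The restriction to continuing smokers is a selection made after randomisation, and it sits beside an intention-to-treat statement in the same section. The (1 + rho)/2 result also assumes randomised groups, so within this subset it is a guide to precision and not a guarantee against bias.

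**Conclusion.** The point holds in limited form. Mann-Whitney cannot make the three-arm comparison for which S. 3.4 names it. The consequence is about 12% family-wise error instead of 5%, conditional on three unadjusted pairwise tests being run.

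On the change-score reading, the analysis is valid under randomisation but less precise than ANCOVA, whose variance is 65%, 75%, 85% and about 97% of the change-score variance at rho 0.3, 0.5, 0.7 and 0.95. That range rests on an assumed correlation and on equal variances at the two times.

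The reach is one listed secondary outcome and two measures that are not listed as outcomes. The correction is worth making and does not bear on the primary result. The restriction to continuing smokers limits how these results can be interpreted more than the choice of test does.

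**What to change.** Replace the sentence in S. 3.4 with wording that does four things:

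1. **Three-group rank test.** Name Kruskal-Wallis in place of Mann-Whitney. For stage of readiness, proportional-odds regression on arm with baseline readiness is an alternative.
2. **Pairwise tests.** Allow pairwise Mann-Whitney only after a significant three-group result. With exactly three arms this ordering keeps the family-wise error for each measure near 5%: if all arms are equal the first test guards the rest, and if one arm differs from two equal ones only one true null hypothesis remains.
3. **FTND and each SEQ-12 subscale.** Use ANCOVA of the 6-month score on arm plus the baseline score, with a 2-degree-of-freedom test of arm. This also settles what is meant by the differences between the two times.
4. **Status.** Label these comparisons exploratory and non-randomised, because they include only men who continued smoking, and add that neither ANCOVA nor Kruskal-Wallis removes that selection.

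The cost is a few lines of analysis text. FTND and self-efficacy are already measured at baseline, baseline readiness is already needed for the planned subgroups, and the SPSS package named in the protocol runs these models. No change to recruitment, visits or the primary analysis is needed.

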#### **S. 3.5. Ethical Considerations**

Ethics approval of the study will obtain from Institutional Review Board (IRB) of the University of Hong Kong. The interventions have no physical impact on the subjects. If the participants have any psychological uncomfortable, like depression or anxiety, professional counselling will be provided to help them to decrease these reactions. And they can drop out this study at any time.

#### **S.4. Significance, Expected result and Implementation**

The results of the study can verify the efficient of the video based smoking cessation intervention for the male smokers preparing to pregnancy, and provide essential complementary information on the baseline of self-efficacy about the smoking cessation for male smokers. Besides, result of this study will provide the evidence that a smartphone video is an efficient media which can improve the feasibility of smoking cessation intervention.

The findings from this study can provide information to the health professionals. Then they can adjust the implementation and policy, and further develop appropriate intervention to take fully advantage of family members to help the smokers to quit smoking more efficiently.

Figure 2. The procedure of data collection

[figure not shown]

### S.5. Chronological outline of research plan

| Time(month)                            | 01
(03/2017) | 02 | 03 | 04 | 05 | 06 | 07 | 08 | 09 | 10 | 11 | 12 | 13 | 14 | 15 | 16 | 17 | 18 | 19 | 20 | 21 | 22 | afterwards |
|----------------------------------------|-----------------|----|----|----|----|----|----|----|----|----|----|----|----|----|----|----|----|----|----|----|----|----|------------|
| Cross-sectional study
Investigation |                 |    |    |    |    |    |    |    |    |    |    |    |    |    |    |    |    |    |    |    |    |    |            |
| Data analysis                          |                 |    |    |    |    |    |    |    |    |    |    |    |    |    |    |    |    |    |    |    |    |    |            |
| Video making                           |                 |    |    |    |    |    |    |    |    |    |    |    |    |    |    |    |    |    |    |    |    |    |            |
| Pilot study
Recruitment             |                 |    |    |    |    |    |    |    |    |    |    |    |    |    |    |    |    |    |    |    |    |    |            |
| Intervention                           |                 |    |    |    |    |    |    |    |    |    |    |    |    |    |    |    |    |    |    |    |    |    |            |
| Follow-up                              |                 |    |    |    |    |    |    |    |    |    |    |    |    |    |    |    |    |    |    |    |    |    |            |
| Data analysis                          |                 |    |    |    |    |    |    |    |    |    |    |    |    |    |    |    |    |    |    |    |    |    |            |
| Study design reversion                 |                 |    |    |    |    |    |    |    |    |    |    |    |    |    |    |    |    |    |    |    |    |    |            |
| Major study
Recruitment             |                 |    |    |    |    |    |    |    |    |    |    |    |    |    |    |    |    |    |    |    |    |    |            |
| Apply intervention                     |                 |    |    |    |    |    |    |    |    |    |    |    |    |    |    |    |    |    |    |    |    |    |            |
| Follow up                              |                 |    |    |    |    |    |    |    |    |    |    |    |    |    |    |    |    |    |    |    |    |    |            |
| Data analysis                          |                 |    |    |    |    |    |    |    |    |    |    |    |    |    |    |    |    |    |    |    |    |    |            |
| Outcome report                         |                 |    |    |    |    |    |    |    |    |    |    |    |    |    |    |    |    |    |    |    |    |    |            |

